### Participant timeline {13}

Table 1 shows the participant timeline.

**Table 1 Tab1:** Participant timeline

	Study period								
	Enrolment	Allocation	Post-allocation						Close-out
Timepoint	Before surgery	Before surgery	During surgery	Postoperative day 1	Postoperative day 3	Postoperative day 5	Postoperative day 7	Postoperative day 30	Postoperative day 90
Enrolment									
Informed consent	** × **								
Eligibility screen	** × **								
Allocation		** × **							
Randomization		** × **							
Interventions									
Tissue samples collection			** × **						
Ketorolac tromethamine		** × **		** × **	** × **				
0.9% saline		** × **		** × **	** × **				
Assessments:									
Vital signs	** × **		** × **	** × **	** × **	** × **	** × **	** × **	** × **
Hematology examination	** × **		** × **	** × **	** × **	** × **	** × **	** × **	** × **
CTA scan of cervical thoracic and abdominal aorta artery	** × **							** × **	** × **
Chest X-ray				** × **	** × **	** × **	** × **	** × **	** × **
Echocardiography	** × **				** × **			** × **	** × **
Adverse events	** × **		** × **	** × **	** × **	** × **	** × **	** × **	** × **
Complications	** × **		** × **	** × **	** × **	** × **	** × **	** × **	** × **

### Sample size {14}

The required sample size was calculated using the PASS (15.0.5) software. The primary endpoint of efficacy was used to calculate the sample size. In the literature, the total death rate of hospitalization after surgery was 25% [7], the incidence of organ malperfusion syndrome was 15–33% [19, 20], permanent dialysis was 2.6% [21], tracheotomy was 8% [22], neurological impairment was 6.9% [22], postoperative mechanical circulatory support was 20% [23], unplanned cardiac reoperation was 4.2% [24], and postoperative cardiac arrest was 0.7–5.2% [25]. Therefore, we assumed that the incidence of composite endpoint events in the control group is 70%, and the incidence of composite endpoint events in the ketorolac group is reduced to 40%. Using PASS (15.0.5) software, when the sample size of the ketorolac group and the control group is 53 cases, this difference can be detected with over 90% confidence. Considering that the loss of follow-up rate is higher than 10%, the final total sample size of this experiment is 120 cases, with 60 cases in the experimental group and 60 cases in the control group.

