### Eligibility criteria {10}

The inclusion criteria are as follows:Patients diagnosed with aTAAD require emergency operation;Patients aged between 18 and 65; andSigning an informed consent.

The exclusion criteria are as follows:Long-term fasting or inability to self eat;History of malignant tumors;Weight < 50 kg;Traumatic aortic dissection;Patients with Marfan syndrome;Unstable vital signs require mechanical assistance or rescue before surgery (IABP, ECMO, LVAD, etc.);Patients required endotracheal intubation before surgery;After admission, patients with consciousness disorder, central nervous system dysfunction, or evidence of cerebral hypoperfusion;Preoperative hematemesis, black or bloody stools, or bowel dilation;Limb ischemia before surgery;Malperfusion syndrome before surgery;Patients who need percutaneous interventions to relieve malperfusion;History of digestive ulcer or chronic gastroenteritis;Dialysis before admission or a history of renal insufficiency;History of liver disease;Allergies to aspirin and non-steroidal anti-inflammatory drugs like ketorolac tromethamine;Chronic inflammatory diseases, autoimmune diseases, or other situations require long-term use of hormones or non-steroidal drugs;No cerebral perfusion during deep hypothermic circulatory arrest;History of Grade 4 surgery or acute myocardial infarction within 90 days;History of cardiac surgery or operations on great vessels;Pregnant and lactating women;Refusing to participate in this clinical trial or sign an informed consent form;Other situations where the subject deems it unsuitable to participate in this project.

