### Outcomes {12}

#### Primary endpoint

Efficacy: death, organ malperfusion syndrome, permanent dialysis, tracheotomy, neurological impairment, postoperative mechanical circulatory support, and unplanned cardiac reoperation.

Safety: gastrointestinal ulceration, gastrointestinal bleeding, gastrointestinal perforation, postoperative hemorrhage (postoperative hemorrhage exceeding 1000 ml within 24 h), renal failure, liver failure, drug allergies, and other severe adverse events following drug administration.

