## Statistical methods

### Statistical methods for primary and secondary outcomes {20a}

Statistical analysis will be performed using SPSS software (version 26.0) and R (× 64 3.5.0). Continuous variables will be presented as mean ± standard deviation. The Kolmogorov–Smirnov test will assess normal distribution. If variables exhibit normal distribution, an independent sample *t*-test will be employed; otherwise, the Mann–Whitney *U* test will be utilized. Categorical variables’ frequency will be expressed as percentages and analyzed using the chi-square test or Fisher’s exact test. It should be noted that we are not conducting an Intention to Treat analysis due to the exclusion of patients with more than 10% missing data. Double-tailed *p*-values and 95% confidence intervals will be reported, with statistical significance defined as *p* < 0.05.

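### The 70% control rate draws on an event outside the primary efficacy endpoint and exceeds what the seven actual components give under independence (59.2–67.9%)

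*Protocol article*

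**What the plan says.** Sample size {14} states that the trial was sized on the primary efficacy endpoint. It then lists literature rates:

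- death 25%
- organ malperfusion syndrome 15–33%
- permanent dialysis 2.6%
- tracheotomy 8%
- neurological impairment 6.9%
- postoperative mechanical circulatory support 20%
- unplanned cardiac reoperation 4.2%
- an eighth item: "postoperative cardiac arrest was 0.7–5.2" per cent

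With no rule for combining them, it continues: "Therefore, we assumed that the incidence of composite endpoint events in the control group is 70" per cent, and "the incidence of composite endpoint events in the ketorolac group is reduced to 40" per cent. The size per arm follows: "is 53 cases, this difference can be detected with over 90% confidence". The total is then raised to 120, or 60 per arm, to allow for loss to follow-up above 10%.

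Primary endpoint defines the efficacy composite with seven components. The list ends with "neurological impairment, postoperative mechanical circulatory support, and unplanned cardiac reoperation", and cardiac arrest is not in it. Cardiac arrest appears as a trial variable only under Safety assessment.

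Statistical methods {20a} says categorical variables are "analyzed using the chi-square test or Fisher’s exact test", two-sided at 0.05.

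**The concern.** The word linking the eight rates to 70% presents the control rate as a consequence of those rates. Two things do not fit. The list contains an event that the endpoint does not, so the endpoint used for sizing and the endpoint defined for analysis are not the same. And no simple way of combining the rates leads to 70%: adding them gives more, and combining them as independent events gives less.

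The control rate matters because the assumed effect is very large, a fall from 70% to 40%. If the true control rate is lower and ketorolac removes the same fraction of events, the absolute difference shrinks and so does the power. A null result could then be read as stronger evidence against benefit than it is.

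A second, smaller matter is that the section speaks of confidence where it means power, and names neither the test nor the alpha behind the figure.

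**Working it through.** **1. Reproducing the plan's figure.** Inputs: 70% and 40% (Sample size {14}); two-sided 0.05 (Statistical methods {20a}); 1:1 allocation (Trial design {8}). The word confidence is read as power.

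Unpooled Z test: n = (1.960 + 1.2816)² × (0.7×0.3 + 0.4×0.6) / 0.3² = 52.54, so 53 per arm. Power at 53 = Φ(0.3/√(0.45/53) − 1.960) = Φ(1.296) = 90.2%. The stated figure is reproduced. The allowance for loss also fits: 53/0.9 = 58.9, so 59, rounded up to 60. Conversely, 53 of 60 allows for 11.7% loss.

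**2. Power with the planned tests, 70% versus 40%.** Pooled chi-square at 53, with mean rate 0.55: Φ((0.3 − 1.960×√(2×0.55×0.45/53)) / √(0.45/53)) = Φ((0.3 − 0.1894)/0.0921) = Φ(1.200) = 88.5%. Exact power was obtained by enumerating all outcomes.

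| Per arm | Pooled chi-square (formula) | Pearson chi-square (exact) | Fisher (exact) |
|---|---|---|---|
| 53 | 88.5% | 87.8% | 83.6% |
| 60 | 92.0% | 92.4% | 89.4% |

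The pooled formula needs 56 per arm for 90%.

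**3. What the cited rates give for the composite.**

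*Plain sum, seven components:* 25 + (15 to 33) + 2.6 + 8 + 6.9 + 20 + 4.2 = 81.7% to 99.7%. With cardiac arrest (0.7 to 5.2): 82.4% to 104.9%.

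*Independence, seven components:*
- malperfusion 15%: 1 − 0.75×0.85×0.974×0.92×0.931×0.80×0.958 = 1 − 0.4076 = 59.2%
- malperfusion 33%: 1 − 0.75×0.67×0.974×0.92×0.931×0.80×0.958 = 1 − 0.3213 = 67.9%

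*Independence with cardiac arrest:*
- lowest: 1 − 0.4076×0.993 = 59.5%
- highest: 1 − 0.3213×0.948 = 69.5%

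So 70% lies 2.1 points above the seven-component maximum under independence, and still 0.5 points above the eight-rate maximum. Adding cardiac arrest moves the independence figure by 0.2 points (67.9% to 68.1%, at 0.7% arrest) to 2.1 points (59.2% to 61.4%, at 5.2%). The malperfusion range moves it by 8.6 points. If events cluster in the same patients, the composite falls below the independence value.

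**4. Effect on power (pooled chi-square).**

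| Control rate | Ketorolac rate at the same ratio (×40/70) | Power at 53 per arm | Power at 60 per arm | n per arm for 90% | Power at 53 per arm if the 30-point difference is kept |
|---|---|---|---|---|---|
| 70% | 40.0% | 88.5% | 92.0% | 56 | 88.5% |
| 67.9% | 38.8% | 86.2% | 90.1% | 60 | 88.3% |
| 59.2% | 33.9% | 75.3% | 80.4% | 80 | 88.6% |

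**The case against.** **The power claim reproduces.** A reader might infer from the chi-square figures that 53 per arm is an arithmetic error and that the stated power is not delivered. The document does not support that. A standard formula gives 53 and 90.2%, the pooled chi-square is within 2 points of 90%, and at the 60 per arm to be randomised it has 92%. Fisher's lower figure is not the expected case either: at 53 per arm and a 55% pooled rate, expected cell counts are about 24 and 29, far from the small counts that usually prompt that test. What remains is that the formula behind 53 is not the planned test and should be named.

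**Overlap may have been considered.** It is tempting to say that the plan ignores overlap. Ignoring it would mean adding the rates, which gives 82–105%. The assumed 70% is below every such sum, so the fair description is that its derivation is not given.

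**The cardiac arrest mismatch is small.** True: it is worth at most 2.1 points. It is an inconsistency to correct, not the main driver of power.

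**The true rate could be higher or lower.** The cited death rate is in-hospital while follow-up runs to 90 days, which could raise the composite. Components that preclude one another, such as an early death before later events, would also push it above independence. In the other direction, Eligibility criteria {10} excludes patients over 65 and several high-risk groups, for example "Malperfusion syndrome before surgery". Whether the cited cohorts had similar exclusions cannot be checked from the article. A reader might go further and infer control rates of 40–50%, with power at 53 per arm of 48–62%. Those rates need strong overlap that the document does not quantify, plus a fixed relative reduction that it does not state.

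**Conclusion.** The point holds as an unsupported and somewhat optimistic input, plus a mismatch between the endpoint sized on and the endpoint defined. From the seven actual components, the control rate is about 59–68% under independence and lower with positive overlap. This treats the cited rates as applicable to the trial population and assumes that components are independent or positively associated.

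The loss of power is conditional. At 53 per arm it is 75–86% if the relative reduction of 40/70 carries over, and about 88–89% if the 30-point difference does. The latter would imply a larger relative effect than the 43% (30/70) already assumed. On the plan's own 70% and 40%, power is adequate: about 88% for the chi-square at 53 per arm and 92% if all 60 are analysed.

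**What to change.** 1. Reconcile Primary endpoint and Sample size {14} on postoperative cardiac arrest, so that the endpoint sized on is the endpoint defined.
2. Restate the control rate as at most about 59–68% from the cited components, say that this assumes independence, and note that positive overlap would lower it. If 70% is kept, give its basis.
3. Replace "this difference can be detected with over 90% confidence" with power for the planned test at two-sided 0.05: about 88% with 53 per arm and 92% with 60 per arm, for 70% versus 40%.
4. Add the sensitivity at 53 per arm: 75–86% for control rates of 59–68% with the relative reduction kept, and about 88–89% with the 30-point difference kept.
5. Optionally, compare the blinded pooled event rate in the 55 patients reported under Trial status with the implied (70 + 40)/2 = 55%. The 95% margin is 1.96×√(0.55×0.45/55), about 13 points. Even the 59.2% scenario implies (59.2 + 33.9)/2, about 47%, so this is only a rough check. Some of these patients may also not have reached day 90 at the reported date.

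The cost is rewording, with one blinded count if wanted. No extra patients are needed. The downside is a less favourable stated power.

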### Recruitment {15}

Commencing from August 2023, all patients with type A aortic dissection (aTAAD) undergoing treatment at our institution will be informed and invited to participate in this clinical trial. The study aims to enroll a total of 120 eligible patients from the cardiothoracic surgery department of Nanjing Drum Tower Hospital within the timeframe spanning August 2023 to December 2026. Our center, renowned for its expertise, conducts more than 250 surgical procedures for aTAAD annually. Anticipating a robust enrollment process, we project the successful recruitment of the targeted 120 patients within the designated timeframe.

## Assignment of interventions: allocation

### Sequence generation {16a}

This study employs a block-randomized treatment allocation strategy to minimize selective bias in treatment assignment. The trial utilizes a block randomization approach, facilitated by SAS 9.4 statistical software, with participants allocated in a 1:1 ratio to the ketorolac and placebo groups. Sequentially numbered random codes are generated based on the “Central Code Random Number Table.” The random number table is provided by qualified professionals. As recruitment is finishing, participants can only obtain a random code, without knowledge of the corresponding medication.

### Concealment mechanism {16b}

This trial employs a double-blind design to ensure the implementation of blinding throughout the experimental process. We conduct medication blinding based on randomized codes. Ketorolac and placebo drugs will be enclosed in identical envelopes. Participants, drug dispensing center staff, and trial personnel will be unable to discern the type of medication based on envelope appearance. Blinding will be accomplished by encoding the experimental and control drugs according to random information and placing them into indistinguishable envelopes. Each coded drug will have an accompanying emergency letter for unblinding in urgent situations. Monitors and researchers must remain blinded throughout, and records of the blinding process will be meticulously maintained.

After obtaining informed consent forms, clinical physicians, responsible for recruiting participants based on inclusion criteria, will sequentially assign random codes. A drug administrator, independent from the study intervention and evaluation, will dispense the drug based on the random code. The drug, enveloped in a standardized cover, will then be administered to the patient. The names and random codes of participants will be recorded and stored by clinical physicians, while the drug administrator will handle drug distribution and retrieval. Records of both dispensing and retrieval will be documented. Until the trial is unblinded, all involved personnel will remain unaware of the grouping of participants.

### Implementation {16c}

Essentially, qualified professionals generate random codes, and a subgroup not involved in medication distribution independently packages and codes the drugs according to these random codes. This ensures a one-to-one correspondence between the random codes and the medications. Upon patient enrollment, the clinical doctor assesses eligibility, and patients are assigned sequential random codes. The medication administrator then dispenses the drugs based on these random codes.

## Assignment of interventions: blinding

### Who will be blinded {17a}

This study adheres to a double-blinded design, ensuring that both the study staff (excluding those engaged in drug preparation) and the patients remain unaware of the treatment assignments.

### Procedure for unblinding if needed {17b}

Emergency unblinding can be performed at any time if patients experience severe adverse events or unexpected worsening of their clinical status, as deemed necessary by the principal investigator or the sponsor. Participants are provided with “In case of emergency” cards, which should be carried at all times during the study and include an emergency phone number. The researcher must record the date, location, reason, person responsible for unblinding, main investigator, and relevant personnel in charge of the drug clinical trial institution. These details should be documented in the case report form (CRF). Subjects who undergo emergency unblinding will be considered as withdrawal cases.

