### Criteria for discontinuing or modifying allocated interventions {11b}

Subjects can withdraw from the study at any time for any reason. Considering the safety of the subjects. When the subject experiences situations where it is not appropriate to continue the study, including worsening of the condition, serious adverse events, poor compliance, experiencing intolerable accidents such as bankruptcy or family misfortune, and unwillingness to sign an informed consent form. Patients can be terminated to continue this study.

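### Emergency unblinding counts as withdrawal, and worsening or a serious adverse event may end participation, so patients can be lost from the analysis because of their outcome

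*Protocol article*

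**What the plan says.** The section on unblinding {17b} gives the trigger: "Emergency unblinding can be performed at any time if patients experience severe adverse events or unexpected worsening of their clinical status", when the principal investigator or the sponsor judges it necessary. It ends with the consequence: "Subjects who undergo emergency unblinding will be considered as withdrawal cases".

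The section on discontinuing or modifying interventions {11b} lists situations in which continuing is not appropriate, "including worsening of the condition, serious adverse events, poor compliance" among them, and concludes: "Patients can be terminated to continue this study". What can end is the study, not just the study drug.

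The primary endpoint section lists "Efficacy: death, organ malperfusion syndrome, permanent dialysis, tracheotomy, neurological impairment, postoperative mechanical circulatory support, and unplanned cardiac reoperation". Its safety list runs from gastrointestinal bleeding, postoperative hemorrhage and renal failure to "other severe adverse events following drug administration".

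The statistical methods {20a} say that "we are not conducting an Intention to Treat analysis due to the exclusion of patients with more than 10% missing data". Section {20c} repeats the deletion rule. No section says that an unblinded or discontinued patient stays in follow-up or in the primary analysis.

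**The concern.** A severe adverse event or a serious deterioration is what this trial sets out to count. The same kind of event is also the reason for classing a patient as withdrawn or ending participation. An outcome can thus become a route out of the data.

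This is a rule that the article states, not a detail left to an analysis plan. If harms that prompt code-breaking are more frequent on ketorolac, more ketorolac patients are exposed to removal and the absolute excess of harm is understated. If removal also differs between arms among patients with events, the relative comparison is biased too, for efficacy as well as safety.

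Withdrawal gains little in exchange. Dosing ends within the first days after surgery, while unblinding is allowed at any time and follow-up runs to day 90. Once dosing is over, classing a patient as withdrawn removes no drug exposure and can only cost outcome data.

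**Working it through.** **1. How a patient could leave the analysis.** Section {17b} makes the unblinded patient a withdrawal, and section {11b} can end participation. Neither section itself removes the patient from the analysis. That step comes from {20a} and {20c}, if the withdrawal pushes missing data above 10%. The article does not define the denominator. If the seven scheduled examination times (before surgery and days 1, 3, 5, 7, 30 and 90) were weighted equally, missing day 90 alone would be 1/7 = 14.3%, and missing days 30 and 90 would be 2/7 = 28.6%. Both exceed 10%. Counted by data item, a late withdrawal could fall below 10%, because the blood samples for ELISA stop at day 7.

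**2. The plan's own figure.** The sample size section assumes 70% against 40%. With two-sided alpha 0.05, power 90% and unpooled variance:

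n = (1.960 + 1.282)² × (0.7×0.3 + 0.4×0.6) / 0.3² = 52.5, so 53 per arm.

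This reproduces the stated 53. The allowance for loss is 60 − 53 = 7 per arm. With 0.70 × 60 = 42 expected control events, removing 7/42 = 16.7% of those patients uses it up.

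**3. Safety illustration.** The article gives no safety event rates or removal fractions, so all are assumed. True events are taken as 12/60 (ketorolac) and 6/60 (placebo). A removed patient leaves both numerator and denominator.

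| Event patients removed (ketorolac / placebo) | Ketorolac | Placebo | Difference | Odds ratio |
|---|---|---|---|---|
| none | 12/60 = 20.0% | 6/60 = 10.0% | 10.0 points | (12/48)/(6/54) = 2.25 |
| one-sixth / one-sixth | 10/58 = 17.2% | 5/59 = 8.5% | 8.8 points | (10/48)/(5/54) = 2.25 |
| half / half | 6/54 = 11.1% | 3/57 = 5.3% | 5.8 points | (6/48)/(3/54) = 2.25 |
| two-thirds / half | 4/52 = 7.7% | 3/57 = 5.3% | 2.4 points | (4/48)/(3/54) = 1.50 |

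**4. Efficacy illustration.** If a fraction f of event patients is removed, the observed rate is p(1−f)/(1−pf) on 60(1−pf) patients. Power is from the pooled Z test: Φ[(Δ − 1.960·s₀)/s₁], with s₀ the pooled and s₁ the unpooled standard error.

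Equal removal, true rates 70% and 40%:

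| f | Control | Ketorolac | Analysed | Power |
|---|---|---|---|---|
| 0 | 70.0% | 40.0% | 120 | 92.1% |
| 10% | 67.7% | 37.5% | 113 | 90.8% |
| 30% | 0.49/0.79 = 62.0% | 0.28/0.88 = 31.8% | 100 | 86.8% |
| 50% | 53.8% | 25.0% | 87 | 79.5% |

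No true effect (70% in both arms), removal in control / ketorolac:

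| Removal | Observed rates | Two-sided type I error |
|---|---|---|
| 10% / 10% | 67.7% / 67.7% | 5.0% |
| 10% / 20% | 67.7% / 65.1% | 6.0% |
| 10% / 30% | 67.7% / 62.0% | 9.4% |
| 0% / 30% | 70.0% / 62.0% | 14.1% |

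**The case against.** The strongest reply is that the text does not say these patients are excluded. Both rules are discretionary, and many primary events, such as a tracheotomy or a reoperation, need not lead anyone to break the code. The reason for unblinding must be entered in the case report form. Data come from the electronic record, medical data from any hospital visit over 90 days are to be recorded, and the adverse event section has all events documented and their incidence calculated. The triggering event may therefore be on file. The removal fractions of a half or two-thirds are high. Equal removal leaves the odds ratio intact, and unequal removal would have to arise although the decision to unblind is taken before the allocation is known.

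Most of this stands, and it limits the claim. A reader might infer that every patient with a primary event is removed, or that the article itself drops withdrawals from the analysis. The documents support neither: the rules are permissive, and exclusion follows only through the 10% missing-data rule, whose denominator is undefined.

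The reply does not show that the patients are protected. Recording an event is not the same as counting it in the primary comparison, and no section keeps a withdrawn patient in follow-up or analysis. Nor does blinding guarantee equal removal: a drug-related harm may prompt code-breaking more readily than other primary events, and such harms need not be spread evenly over the arms.

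**Conclusion.** The point holds as a defect in stated rules: sections {17b} and {11b} do not separate breaking the blind or stopping study drug from leaving the study. With {20a} and {20c}, they allow selective, outcome-dependent removal.

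The size is unknown. On assumed safety rates, a 10-point excess shrinks to 8.8, 5.8 or 2.4 points depending on how much is removed and how evenly. Equal removal distorts the absolute difference and loses precision but leaves the odds ratio at 2.25.

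For efficacy, a reader might infer that any removal biases the result toward ketorolac, and the calculations do not support that. Equal removal of up to 30% leaves the difference near 30 points and mainly costs power (92.1% to 86.8%). Type I error rises, to between 6% and 14% in the three unequal scenarios shown, only when removal differs by arm.

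The sample size of 53 per arm is not at fault here. The point is worth settling before the interim analysis at 60 patients, since 55 had been included by 20 March 2024 and follow-up that has lapsed may not be fully recoverable.

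**What to change.** Replace the last sentence of {17b} with: *Emergency unblinding does not end follow-up or remove the patient from analysis; the triggering event is counted, follow-up continues to day 90 unless consent for it is withdrawn, and the patient is analysed in the allocated group.*

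In {11b}, state that stopping study drug for any reason is separate from leaving follow-up and analysis. Leave unchanged when clinicians may unblind or stop the drug.

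Amend {20a} and {20c} so that these patients are not deleted from the primary analysis. Without this, the first two changes would conflict with the deletion rule. Report unblinded and discontinued patients by arm.

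The cost is a protocol amendment, probably a substantial one under section {25}, with notification of the ethics committee and competent authority and a registry update. Records must also be retrieved for any patient already withdrawn. Continued follow-up uses visits already planned.
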